### Quantifying the Direct and Indirect Impact of Risk Factors on Disease

We will use repeated measure mixed-effect modeling to quantify the direct effects of microbiome on risk of disease while adjusting for clinical factors. We will use case as the random effect and adjust for autocorrelation in the response using appropriate correlation structures in the model. The applicants have used this approach extensively to investigate the epidemiology of food-borne pathogens (92). We will use an SEM approach to quantify direct and indirect effects of risk factors on the incidence of disease. We will develop a set of models that characterize the relationship between clinical factors, the changes in gut microbial community types, developmental stage (postnatal and postmenstrual age), and comorbidities associated with disease onset and then challenge the model with the data derived from the laboratory and clinical data collection (93).

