### Overview of the SIFT and ELFIN Trials

Speed of increasing milk feeds trial and ELFIN trials are funded by the HTA and managed by the National Perinatal Epidemiology Unit Clinical Trials Unit, Oxford, UK.^3^ Both trials recruit very preterm infants (<32 weeks gestation) in the first few days after birth while receiving care on a neonatal unit. The trial interventions complete prior to hospital discharge, although follow-up for SIFT continues until 2 years corrected age. SIFT recruited 2,804 infants and is powered to detect a clinically important difference in disability-free survival at 2 years, as well as having adequate power to detect a difference in the rate of the key short-term outcomes NEC and LOS. Infants were enrolled when stable, tolerating some milk (but less than 30 ml/kg/day), and when the attending clinician was ready to start increasing the amount of milk feeds. Infants were randomized to increases in milk feeds of either 18 or 30 ml/kg/day. Infants from multiple pregnancies (twins, triplets, etc.) were corandomized to the same treatment arm. It was anticipated that the speed of milk feed increases would result in full feeds (defined as at least 145 ml/kg/day) being achieved about 4 days later in the slower arm. This affects the duration of central venous access and use of parenteral nutrition, although this was not mandated in the SIFT protocol and therefore is likely to affect two key risk factors for LOS. The speed of milk feed increases may also affect exposure to breast milk in the first few days of life, a further risk factor for both LOS and NEC. SIFT is a trial of comparative clinical effectiveness and recognizes the possibility that there might be competing outcomes, i.e., there may be opposing impacts on NEC and LOS between the two trial arms (15). Hence, the use of disability-free survival as an outcome that takes this possibility into account. In addition, if there are no differences in key clinical outcomes (including neurological development), then data collected for health economic analyses may determine which regime is adopted in clinical practice.

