The ELFIN trial is evaluating whether supplemental bovine lactoferrin added to milk feeds affects the rate of sepsis and is powered to detect a clinically important reduction in the primary outcome (LOS) from 18 to 13% and will recruit 2,200 infants. Infants are randomized to receive either bovine lactoferrin (150 mg/kg/day) or placebo 150 mg/kg/day (sucrose) both added to milk feeds. The RCT is blinded using masked pots containing the investigational medicinal product (IMP). Unlike SIFT, infants from multiple pregnancies are randomized independently. An internal pilot phase started in June 2014 in five sites, with recruitment to the main trial commencing in July 2015. The trial is currently in progress and anticipated to complete recruitment toward the end of 2017. Further details of the trial are available (16).

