### Sample Size Estimates

Sample size requirements for each element of this study have been evaluated and are based on both published data and practical/logistical aspects from our existing work and that from other published studies. These considerations include
The duration, estimated start time, and recruitment rate for ELFIN, along with the estimated start date for MAGPIE and logistical issues in establishing recruitment from 10 hospital sites.The trial efficacy and disease event rate will not be known until the main trial completes. The incidence of NEC (Bell stage 2 or greater) is expected to be 5–10% and for LOS <20%, and some infants will have both diseases. Recruiting 480 infants will identify between 70 and 100 “disease” cases, 10–20 cases requiring gut surgery, and provide well sampled “non-diseased” infants with varying clinical risk factors, exposures, and outcomes.VOC analysis may identify several individual compounds; in our recent paper publishing the methodology, we show that on average 31.3 ± 10.5 (mean and SD) VOCs were identified per sample (82). At a power of 80%, and two-sided significance at the 5% level, we would need 50 infants per trial intervention group to show an increase in 5 VOCs. The SD for each sample was 2.9 ± 1.3 compounds and on average 90% of the VOC abundances showed a coefficient of variation smaller than 30%. Our data also showed in a study of 13 infants, which VOC number in healthy neonates significantly increased with age (0.49 extra VOCs per day 95% CI 0.12–0.86), a trend not seen in those who developed NEC (64).Microbiomic data complexities means that the sample size necessary to evaluate the actions of different interventions and the incidence of disease is dependent on effect size, the number of interacting factors, and their correlation. For a power of 80% to detect a 50% difference in community profile patterns arising from a categorical descriptor of microbial community variation, using a two-sided test at a significance level of 5%, the study needs ~200 samples. In our previous studies (1) 12 twin pairs analyzed (gut microbial profiling) using PLS-DA showed highly significant correlations between pairs (53) and (2) examination of 136 samples from 32 patients (*n* = 20 NEC or LOS) showed significant differences (*p* = 0.002) in microbiomic patterns between diseased and healthy individuals (24).Using immunohistochemical data from our group (83), and assuming that any differences between disease and control will be greater than those in healthy individuals, and using a two-sample *t*-test, our proposed sample size of 20 would give 80% power to detect a difference of 0.66 (66%) in cells/crypt cross section at a significance level of 5% and an approximated SD of 0.5 (50%).Mixed-effects models, which we propose for modeling the direct effects of the microbiome on disease risk, are economical with power because the residual variance of these models is smaller since some of it is accounted for in the random effect. Using the method by Cohen (84), we calculate that a GLM would have a power of 82% with 10 predictors and 50 for a “large” effect size (*f*^2^ = 0.35, *R*^2^ = 0.51) at the 5% level of significance, and a power of 47% for a “medium” effect size (*f*^2^ = 0.15, *R*^2^ = 0.36) at the 5% level of significance. With *n* = 100 the calculated powers are 99% for a large effect size and 74% for a medium effect size. Including random effects in the GLM would increase power at the same effect size or conversely permit smaller effect sizes at the same power. The power analysis of an SEM is altogether more complex because it relies on the goodness-of-fit criteria selected for the model. Power at the model level may be low when there are few model degrees of freedom even for a reasonably large sample size; requiring greater than 100 samples if there are fewer than 20 model degrees of freedom (85). We will supplement these models where needed using a Bayesian SEM approach.

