
### Statistical Analysis

There are three major modeling issues that have to be addressed in this analytical pathway:
(i)the multivariate nature of the microbiome and metabolome, and data generated from immunohistochemistry;(ii)the longitudinal/developmental component in the neonate, which will lead to repeated measures of disease state and microbiome on the same individuals, and(iii)the interdependence and interactions between different predictors, which may have both direct and indirect effects on incidence and progression of disease.

The analytical approach used in this study will focus on modeling the relationship between putative risk factors, trial interventions, and incidence of NEC and LOS from longitudinal data capturing variation in both risk factors and disease through time, and the any differences in non-diseased cases between trial arms. We will use a progressive modeling strategy based on combining multivariate analyses of micro- and metabolomic immunological data, with mixed-effect modeling of outcome in relation to drivers of disease; and finally, mixed-effect SEM to quantify the importance of interacting factors and drivers. Specifically, we will
(i)quantify the impacts of individual risk factors in causing disease;(ii)quantify the effects of direct and indirect risk factors on disease;(iii)quantify the dynamics of pathogens, the neonatal microbiome, the immune response, and their impact on outcomes, and(iv)identify the impacts of trial interventions and clinical management on the drivers and disease.

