## Anticipated Results from Analysis of Microbiome and Metabolome

We will use multivariate ordination techniques to summarize and visualize the major trends in variation in microbial community composition of infants’ stool collected. The analyses will identify those taxa most closely associated with microbiome change through time. We will use canonical ordination to quantify the impacts of other covariates (diet, age, and interventions) on the microbiome composition. We will identify key microbial taxa in the ordination space that capture the trend in variation in relation to disease and use these with the results of the ordination as input variables for the subsequent mixed-effect and SEM analyses below. To ensure the results are not spurious, the observed differences in metabolomic profiles will be validated by permutation testing in MetaboAnalyst 3.0 (86). Where appropriate, significance of categorical variables were determined using the non-parametric Mann–Whitney test for two category comparisons or the Kruskal–Wallis test when comparing three or more categories (87) and all *p*-values were adjusted for multiple comparisons with the false discovery rate algorithm (88).

MixOmics (89) will be implemented to determine the correlation between the relative abundance of the dominant bacterial taxa from 16S rRNA gene sequencing and the intensity of metabolites of interest by sparse partial least squares regression (90). Longitudinal and network analyses will facilitate investigations into the directionality of any observations. Tax4Fun (62) will be used to infer the metabolic potential of the microbiome based on the 16S data. Model-based integration of metabolite observations and species abundances will then be applied to determine biologically feasible correlations between the inferred bacterial KEGG orthology and the resulting metabolites of interest (91). This will determine which metabolites are likely to be bacterial derived. It is important to note that in the course of data generation, new tools are likely to emerge that can perform distinct analyses on multi-omic data. Where appropriate we will incorporate such tools where they are likely to (1) outperform existing tools and/or (2) allow novel analyses to be performed.

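### No family level is named although SIFT siblings share an arm, and the microbiome sizing of about 200 samples makes no allowance for repeated stools from one infant

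*Protocol article*

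**What the plan says.** **Models.** Under Quantifying the Direct and Indirect Impact of Risk Factors on Disease, the article specifies repeated-measures mixed models: "We will use case as the random effect and adjust for autocorrelation in the response using appropriate correlation structures in the model". I read case as the infant. No mother or sibling-set level is named there. Multiple birth is also absent from the adjustment factors listed under Plan for Interim Statistical Analyses (age, sex, gestation, feed and antibiotic exposures).

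**Siblings.** Under Overview of the SIFT and ELFIN Trials, SIFT infants from multiple pregnancies "were corandomized to the same treatment arm", whereas in ELFIN "infants from multiple pregnancies are randomized independently". Under Sample Size Estimates, the group's earlier work is cited: "12 twin pairs analyzed (gut microbial profiling) using PLS-DA showed highly significant correlations between pairs". No coefficient is given.

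**Sizing.** The same section states: "For a power of 80% to detect a 50% difference in community profile patterns arising from a categorical descriptor of microbial community variation", two-sided at 5%, "the study needs ~200 samples". It mentions no within-infant correlation. Aims and Objectives lists four scheduled stool windows and up to seven daily stools before disease onset. Procedures—Summary lists five windows.

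**Repeated measures.** Statistical Analysis acknowledges the longitudinal component, "which will lead to repeated measures of disease state and microbiome on the same individuals".

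**The concern.** There are two separate issues of dependence.

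The first is between siblings. Where siblings share an arm, the randomised unit is the sibling set. If their gut profiles are also correlated, an analysis that treats them as independent infants understates the standard error of the arm effect. The article supplies both facts (co-allocation and twin correlation), but the model structure it names uses neither. A random effect for the infant absorbs repeated stools from one baby; it does not absorb correlation between two babies of one mother.

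The second is within the infant, in the sizing. Five correlated stools from one infant carry less information on a difference between infants than five stools from five infants. A power statement that counts samples and gives no correlation will overstate power unless each sample comes from a different infant.

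At stake are a somewhat raised false-positive rate in the SIFT arm comparison and a stated 80% power that may not apply to the comparison a reader has in mind.

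**Working it through.** **1. Can the figure of about 200 be reproduced?** Not from the article, which gives no baseline proportion, SD or number of community classes. With independent observations, 80% power and two-sided 5%, the total for two proportions differing by 50% in relative terms depends on the assumed baseline:

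- 20% vs 30%: 588
- 30% vs 45%: 326
- 40% vs 60%: 194 (214 with continuity correction)

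A difference of 25% vs 50% gives 116, and a standardised mean difference of 0.5 gives 126. The figure of 200 is thus compatible with an independent-observations formula, but only under a chosen baseline.

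**2. Power of 200 samples with repeated stools.** The number of stools per infant, m, comes from the article: 136/32 = 4.25 in the group's earlier study, five planned windows, up to seven stools before disease. The ICC is not given and is assumed. The design effect is DE = 1 + (m − 1) × ICC. The effective number is 200/DE. Power for an infant-level contrast is Φ(2.80/√DE − 1.96), which returns 80% at DE = 1.

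| m | Infants (200/m) | ICC | DE | Effective n | Power |
|---|---|---|---|---|---|
| 4.25 | 47 | 0.1 | 1.32 | 151 | 68% |
| 4.25 | 47 | 0.7 | 3.27 | 61 | 34% |
| 5 | 40 | 0.3 | 2.2 | 91 | 47% |
| 5 | 40 | 0.5 | 3.0 | 67 | 37% |
| 7 | 29 | 0.3 | 2.8 | 71 | 39% |
| 7 | 29 | 0.5 | 4.0 | 50 | 29% |

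To keep an effective 200 at m = 5 and ICC 0.5, 200 × 3.0 = 600 samples would be needed.

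**3. SIFT arm comparison.** About 100 infants (Introduction). The share in complete pairs is assumed at 30% (70 singletons and 15 pairs), and the sibling ICC at 0.5–0.7. With co-allocated pairs, DE = 1 + share × ICC, and the true type I error of an analysis ignoring siblings is 2[1 − Φ(1.96/√DE)].

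- ICC 0.5: DE = 1.15; true SE larger by √1.15 = 1.07; type I error 6.8%. Simulation (20,000 runs): 6.7%.
- ICC 0.7: DE = 1.21; true SE larger by √1.21 = 1.10; type I error 7.5%. Simulation: 7.5%.

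Over a wider range (20–40% in pairs, ICC 0.3–0.8), DE is 1.06–1.32, the true SE is 3–15% larger than the naive one, and type I error is 5.7–8.8%.

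**4. ELFIN arm comparison.** The same simulation (100 infants, 30% in pairs) with siblings allocated independently gives 5.3% (ICC 0.5) and 4.7% (ICC 0.8): no inflation.

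**5. Neonatal unit.** Simulated arm comparison with 100 infants, ten units and unit ICC 0.05–0.2: about 5% when allocation is not balanced within unit, and 4.8% down to 2.8% when it is. Leaving unit out does not make this standard error too small.

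**The case against.** The strongest reply is that this is a condensed article with no analysis plan shown. Further random-effect levels and the unit of each test are commonly left to that plan, and naming the infant does not exclude a mother term. The cited sentence also concerns models of disease risk, whereas co-allocation matters for arm comparisons. This has weight and keeps the point modest. It does not remove it: the article fixes one random effect, reports the sibling facts itself, and lists the impact of the trial interventions among the aims of the same modelling strategy. The power statement is a stated figure, not an omission.

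On sizing, the planned analysis may exceed 200 independent infants: about 70–100 diseased plus up to 200 non-diseased. For the arm comparison, 25–50 infants per arm at five windows gives 250–500 samples. At ICC 0.3–0.5 (DE 2.2–3.0) that is an effective 83–114 at the lower end and 167–227 at the upper. The defect therefore lies in the stated figure; it does not show that the study as a whole is underpowered.

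A reader might also infer several stronger claims that the article does not support:

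- *The models ignore repeated stools.* They do not. Repeated measures are named as a modelling issue and met with the infant random effect and a correlation structure.
- *The rank tests are run on samples.* The Mann–Whitney "test for two category comparisons" is named without a unit of analysis, and so is the permutation testing. One value per infant per window fits the text equally well, and the interim comparison selects samples from a single window.
- *All sizing counts samples.* The volatile-compound calculation counts infants.
- *Omitting neonatal unit makes arm-comparison standard errors too small.* It does not (step 5), and the SIFT samples come from one site.

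**Conclusion.** The point holds in two limited parts.

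First, the named models have no family level, although SIFT siblings share an arm and the article reports twin correlation. The consequence is confined to the arm comparison in about 100 SIFT infants and is modest: type I error of about 6.7–7.5% if 30% of infants are in pairs and the sibling ICC is 0.5–0.7. Neither input is in the article. The ELFIN arm comparison is not inflated. For comparisons of diseased and non-diseased infants, the direction depends on how siblings fall across the groups and on the matching, and cannot be determined from the text.

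Second, 80% power from about 200 samples holds for an infant-level contrast only if they come from about 200 different infants. At five stools per infant and an assumed ICC of 0.3–0.5 it is about 47–37%. Even at ICC 0.1 and 4.25 stools it is 68%.

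Standard errors that are too small throughout the plan would be too strong a conclusion.

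**What to change.** 1. Add a random effect for mother (multiple set) to the mixed models, at least in every model that includes SIFT infants. In ELFIN it is optional for validity and can only gain precision.
2. Restate the microbiome sizing as about 200 infants, or give the stools per infant, the assumed ICC, the design effect and the resulting power, and say which comparison the figure serves.
3. As a low-cost safeguard, state that rank tests use one value per infant per window, and that permutation moves whole infants (whole sibling sets in SIFT).

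The cost is wording. SIFT allocated by sibling set, so the link between siblings should be available from the trial. The downside is slightly larger standard errors in SIFT comparisons and a less favourable stated power.

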### Plan for Interim Statistical Analyses

The MAGPIE study funder (NIHR) and the project team agreed that it would be appropriate to conduct a futility-type analysis to ensure there are measurable impacts on the microbiome after ~150 (of the total planned 480) infants have been recruited, and prior to commencing further analysis of the microbiome and metabolome. The ELFIN study is blinded so any laboratory and statistical analysis of anonymized samples while recruitment continues will be conducted by investigators blinded to trial interventions. Blinding to trial intervention arm will also be maintained while gut tissue is examined.

For the interim analyses we will
Select samples taken before disease onset at around 7–10 days after commencing the trial IMP (lactoferrin or placebo) in up to 60 infants per trial group so as to compare and assess microbial community changes between trial groups. Because other risk factors are also associated with disease (e.g., gestation, postnatal age, etc.), we will use progressive model building that investigates microbial community dynamics in relation to these covariates.Use multivariate ordination and classification approaches to quantify trial intervention group differences in gut microbial communities. This will (i) quantify the variation in microbial community composition before disease onset and (ii) develop suitable covariates describing microbial community variation for inclusion in statistical analysis as risk factors for disease.Use unconstrained ordination to investigate trends in community composition and to identify those microbial taxa from the NGS data that contribute most to community variation. These axes may be used as covariates in the subsequent analysis.Use constrained ordination to investigate the impact of trial intervention group on community variation prior to disease onset.Use divisive classification approaches to identify classes of microbial community among the cases. This will create a suite of categorical descriptors of community composition. Higher level community descriptors (diversity, evenness, rate of change in ordination score) will be derived in case the overall structure of the community is an important driver.In the interim analyses, we will determine whether there is any effect on the total microbial community differences or on individual bacterial taxa using MANOVA and consider a difference in the microbial community of *p* < 0.05 to be proof an effect. If the *p* value is between 0.05 and 0.1, we will consider this to be strong evidence of a likely effect, where statistical significance might subsequently be achieved in an analysis with larger numbers and/or greater numbers of diseased or high risk cases and will complete the study as planned. Regression models and SEM will adjust for potential confounding variables such as age, sex, gestation, and feed and antibiotic exposures.

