## Procedures—Summary

We will
Recruit at least 480 infants from up to 10 neonatal units in the UK enrolling infants to ELFIN.Identify stored samples from infants recruited to SIFT (one site only).Collect a daily stool and urine sample from MAGPIE infants until hospital discharge (average duration 40–50 days) or transfer back to local neonatal unit.Retrieve any residual resected gut tissue of enrolled infants who undergo intestinal surgery.Identify samples which are the most:
*informative*—based on trial intervention and disease presence;*comprehensive*—consistency of daily sampling;*representative*—balanced for trial intervention and other key factors, e.g., gestation, breast milk exposure.Samples to be analyzed will include
*all diseased cases*: infants who meet the SIFT and ELFIN internationally agreed predefined case definitions of confirmed NEC or LOS following review at Blinded Endpoint Review Committee;*non-disease cases*: infants who do not develop NEC or LOS, selected using matching algorithms to ensure trial intervention and risk factor coverage.The samples analyzed will focus on the early postnatal period when trial intervention differences will be greatest: e.g., day 0—3, 6–8, 9–11, 13–15, and 20–22 in ~25–50 infants per trial intervention arm. While we aim for daily sampling we recognize this will not always be achieved due to the complexity of the NICU working environment, combined with the fact that many sick infants do not pass a stool every day. We will also analyze samples at additional time points as necessary to ensure a daily sample is analyzed for up to 7 days before diagnosis in all diseased cases and match these to non-disease controls.Analyze samples for

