#### Necrotizing Enterocolitis

Necrotizing enterocolitis may be diagnosed at surgery, at postmortem or clinically and radiologically: at least one of the following clinical signs present: bilious gastric aspirate or emesis, abdominal distension, or occult or gross blood in stool AND at least one of the following radiological features: pneumatosis intestinalis, hepatobiliary gas, or pneumoperitoneum. Infants who satisfy the definition of NEC but at surgery or postmortem have a “focal gastrointestinal perforation” will not be coded as having NEC.

All diseased cases meeting the predefined case definition of NEC or LOS will have samples analyzed (expected total ~70–100 infants). Samples from up to 200 non-diseased cases will be selected to ensure sufficient coverage of intervention arms using matching algorithms and coverage of other clinical risk factors and outcomes. We will also analyze samples from non-diseased cases to determine microbiomic and metabolomic profiles between trials arms.

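### A futility-type interim counts p < 0.05 as proof of an effect although the same contrast can be tested again at the end, and the stated per-arm number does not fit the larger-numbers rationale

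*Protocol article*

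**What the plan says.** **Interim.** Under Plan for Interim Statistical Analyses, the funder and project team agree a futility-type analysis "after ~150 (of the total planned 480) infants have been recruited". It takes samples from before disease onset, about 7–10 days after the start of lactoferrin or placebo, "in up to 60 infants per trial group so as to compare and assess microbial community changes between trial groups". A MANOVA p below 0.05 for the microbial community is taken as proof of an effect. With a p between 0.05 and 0.1, the plan sees an effect as strongly suggested and completes the study. The stated reason is this expectation: "where statistical significance might subsequently be achieved in an analysis with larger numbers and/or greater numbers of diseased or high risk cases". No action is written for p above 0.1.

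**Final numbers.** Procedures—Summary introduces the early-period samples this way: "The samples analyzed will focus on the early postnatal period when trial intervention differences will be greatest: e.g., day 0—3". It goes on to list four further day windows, "in ~25–50 infants per trial intervention arm". The section defining necrotizing enterocolitis (NEC) gives the wider analysis set. All diseased infants are included (about 70–100). In addition: "Samples from up to 200 non-diseased cases will be selected to ensure sufficient coverage of intervention arms using matching algorithms". The same paragraph says that non-diseased infants will also be used to compare trial arms. Sample Size Estimates has one arm-level calculation, for volatile organic compounds (VOCs): "we would need 50 infants per trial intervention group to show an increase in 5 VOCs".

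**Error control.** The section on anticipated results from the microbiome and metabolome applies a false discovery rate adjustment to p-values. That addresses many comparisons at one time, not the same comparison at two times.

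**The concern.** Two features of the printed rule do not fit together.

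First, a futility look should answer only whether to go on. Here a p below 0.05 also settles the scientific question, and the same lactoferrin–placebo contrast remains open to a second 5% test. The article does not say which result stands if the two disagree. An interim result taken as proof could be followed by a non-significant final result, or the reverse, and either could be reported as the finding.

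Second, the middle zone is justified by larger numbers later, but the only per-arm figure attached to the early-period samples (25–50) is below the interim's 60. If that were the final comparison, a borderline interim result would tend to stay non-significant because precision falls. At stake are the credibility of the mechanistic arm claim and the reason for continuing after a borderline interim.

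**Working it through.** **Inputs.** Interim: up to 60 per group (Plan for Interim Statistical Analyses). Early-period samples: about 25–50 per arm (Procedures—Summary). Analysis set: up to 200 non-diseased and about 70–100 diseased infants (NEC definition). SIFT samples available: around 100 babies (Introduction). The interim and early-period counts are stated without a calculation, so there is no figure of the plan to reproduce for this point. A single two-group z-test stands in for MANOVA throughout.

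**1. Final size per ELFIN arm allowed by the analysis set**
- Non-diseased only, all from ELFIN: 200/2 = 100.
- With diseased infants: (200 + 70)/2 = 135 to (200 + 100)/2 = 150.
- If about 100 of the total are SIFT infants (assumption; the split is not stated): (270 − 100)/2 = 85 to (300 − 100)/2 = 100.

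The working range is therefore about 85–150. These are ceilings, because the 200 is an upper limit and each infant needs a usable stool in the window.

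**2. Size at which a borderline interim reaches 0.05.** For the same observed effect, z scales as z₂ = z₁√(n/60). For interim p = 0.10, z₁ = 1.645, so n = 60 × (1.960/1.645)² ≈ 85 per arm. For interim p = 0.07, z₁ = 1.812, so n = 60 × (1.960/1.812)² ≈ 70.

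Projected final p at the same observed effect:

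| Final n per arm | interim p = 0.05 | interim p = 0.075 | interim p = 0.10 |
|---|---|---|---|
| 25 | 0.21 | 0.25 | 0.29 |
| 50 | 0.074 | 0.104 | 0.133 |
| 85 | 0.020 | 0.034 | 0.050 |
| 100 | 0.011 | 0.022 | 0.034 |
| 135 | 0.003 | 0.008 | 0.014 |
| 150 | 0.002 | 0.005 | 0.009 |

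**3. Chance that interim p = 0.07 becomes final p < 0.05.** If the final set contains the interim infants and the observed trend continues, final z has mean 1.812√(n/60) and SD √(1 − 60/n).
- n = 85: mean 2.157, SD 0.542, chance 64%.
- n = 100: mean 2.339, SD 0.632, chance 73%.
- n = 135: mean 2.718, SD 0.745, chance 85%.
- n = 150: mean 2.865, SD 0.775, chance 88%.

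If instead the final were 50 of the same 60 infants per arm, the mean would be 1.812√(50/60) = 1.654 and the SD √(1 − 50/60) = 0.408, giving 23%. With 25 of the 60 it would be 15%.

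**4. Type I error of a claim at either look.** Under no effect, the two z-statistics are bivariate normal with correlation √(n_small/n_large). The stopping column is P(p₁ < 0.05, or 0.05 ≤ p₁ < 0.10 and p₂ < 0.05). The other is P(p₁ < 0.05 or p₂ < 0.05).

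| Final n per arm | Correlation | Stops at interim p ≥ 0.10 | Does not stop |
|---|---|---|---|
| 25 of the 60 | 0.645 | 5.7% | 8.6% |
| 50 of the 60 | 0.913 | 6.1% | 6.9% |
| 100 | 0.775 | 5.9% | 8.0% |
| 135 | 0.667 | 5.8% | 8.5% |
| 150 | 0.632 | 5.7% | 8.6% |

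**The case against.** A reader might infer that the final arm comparison must be smaller than the interim, so that deferring a borderline result cannot work and only buys a second 5% test. The documents do not support that.
- The 25–50 figure follows an example of five day windows and describes where sampling will focus. It does not fix the final comparison.
- The NEC definition section allows a larger set, and about 330 of the 480 infants are recruited after the interim. No passage says the final set is a subset of the interim infants, so the 15–23% figures describe only the least favourable reading.
- Up to 60 is itself a ceiling.
- The deferral also names more diseased or high-risk cases, and the final analysis has repeated samples per infant.
- The study is exploratory, the look is futility-type, and with stopping at p ≥ 0.10 the error is close to nominal.

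All of this stands. It is also fair that a condensed article may leave interim and final error control to a fuller document.

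It does not remove the point. The article itself prints the rule that an interim p below 0.05 is proof, and it prints the per-arm figure that sits below the interim ceiling. The larger final set is permitted rather than stated. One reading still gives a small final: if all of about 100 SIFT infants were non-diseased and counted within the 200, and only non-diseased infants were compared, ELFIN would keep (200 − 100)/2 = 50 per arm. The Statistical Analysis section does speak of arm differences in non-diseased infants, so this reading is not excluded.

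**Conclusion.** The point holds in a limited form and should be corrected. The interim rule turns a continue-or-stop look into a claim at full 5%, with the same contrast open to a second test. The inflation is modest: about 5.7–6.1% if the study stops at interim p ≥ 0.10, which the text implies but does not state, and 6.9–8.6% if it continues regardless. Whether the larger-numbers rationale works depends on a number the article does not settle. At 25–50 per arm it fails; at about 85–150 it works, with a 64–88% chance of reaching significance from an interim p of 0.07.

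These results assume one 7–10 day sample per infant, equal arms, a one-degree-of-freedom test in place of MANOVA, 60 infants per arm at the interim and, for the 64–88%, interim infants included and the observed trend continuing.

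**What to change.** **In Plan for Interim Statistical Analyses:** state that the interim yields a continue-or-stop decision only, write out what follows from p ≥ 0.10, and drop the reading of p < 0.05 as proof. State that the between-arm claim is made once, at the final analysis, at 5%.

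**In Procedures—Summary and the NEC definition section:** reconcile the numbers. State that the final 7–10 day lactoferrin–placebo comparison includes all interim infants plus every later ELFIN infant with a sequenced pre-disease stool in that window. Give the expected number per ELFIN arm after setting SIFT infants apart, and keep about 25–50 per arm for the five-window series only.

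**Cost:** wording, plus at most some extra single-time-point 16S runs. The price in inference is that no efficacy claim can be made from the interim.
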